### Secondary Efficacy Outcomes

#### Structured Imaging Report

The structured report (see Table S1 in Multimedia Appendix 1) is completed following the surgical procedure and serves as a synthesis of direct intraoperative findings and preoperative DTI results. During surgery, an experienced colorectal surgeon meticulously explores the lesion and documents the key anatomical conditions. These surgical observations are then integrated with the preoperative DTI interpretations provided by a senior radiologist to finalize the report collaboratively. It is important to clarify that this report is compiled postintervention and therefore does not inform real-time intraoperative decisions. To ensure consistency, all participating surgeons and radiologists received standardized training on the reporting items and definitions prior to the study. To assess inter-rater reliability, a subset of the completed reports will undergo independent review by a second surgeon who remains blinded to the initial assessment.

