### Objectives of the Study

The primary goal of this study is to use DTI to delineate the relationship between the internal opening, the degree of infection and infiltration, the extent of the abscess, and the erosion of perianal tissues and muscles in patients with perianal abscesses. This approach aims to develop an accurate imaging evaluation method for diagnosing the disease, explore the application value of DTI in the diagnosis of perianal abscesses, and improve the accuracy of preoperative evaluation, as well as reduce the damage to the anal sphincter. Ultimately, these efforts aim to reduce the recurrence rate and improve the prognosis and quality of life for patients.

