### Treatment Plan

Both groups undergo an identical perianal MRI protocol on the same 3.0-T scanner using a 16-channel abdominal phased-array coil, with all participants scanned in the supine position. The sole distinction between the 2 imaging protocols lies in the diffusion-weighted sequence: the control group receives conventional DWI, whereas the intervention group undergoes DTI. Crucially, both groups receive intravenous gadolinium-based contrast agent (GD-DTPA) and subsequent identical postcontrast sequences. All remaining sequences, including T1-weighted, T2-weighted, and fat-suppressed T2-weighted imaging, are standardized across groups.

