### Statistical Plan

All analyses are prespecified. The primary analysis will follow the intention-to-treat principle. For the primary outcome, the 6-month recurrence rate will be analyzed using binary logistic regression, with results reported as an adjusted odds ratio and 95%
CI. Any clinically relevant baseline imbalances will be included as covariates, and missing recurrence data will be handled using multiple imputation. Secondary outcomes will be analyzed as follows: categorical items from the structured report will be compared using chi-square test or Fisher exact test; continuous structured report items will be compared using independent samples *t* tests or Mann-Whitney *U* tests, depending on normality; postoperative visual analog scale pain scores will be evaluated with a linear mixed model to assess group, time, and interaction effects, with results expressed as estimated marginal means and mean differences with 95%
CI; and inflammatory markers and Wexner incontinence scores will be compared at follow-up using *t* tests or Mann-Whitney *U* tests. To control for type I error across secondary outcomes, the false discovery rate procedure will be applied. Prespecified sensitivity analyses
using the per-protocol population and subgroup analyses
stratified by abscess complexity will also be performed. All statistical analyses
will be conducted using SPSS software (version 22.0), and statistical significance will be defined as a 2-sided *P* 
value <
.05
.

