In this trial, 90 participants are being enrolled and divided into 2 groups, a DTI group and a conventional MR group, based on randomization performed before enrollment. “The primary variable, recurrence rate, and secondary variables, including structured reports, pain scores on postoperative days 3 and 7, peripheral inflammatory factors, and assessment of anal function, are being assessed at 6 months after surgery.” To ensure accurate and specific information, a structured report on the extent of perianal abscess infection based on DTI images is being prepared by both anorectal physicians and radiologists. Surgeons experienced in examining and operating on the lesions can provide valuable insights into the actual situation of the patient during surgery. By using a structured report, we aim to determine whether the test under consideration is effective and which of the 2 tests is more effective.

Although the recurrence rate of perianal abscesses after surgery is influenced by numerous factors, there is no doubt that the accuracy of the examination can greatly improve the success rate of surgery [29]. Currently, surgical treatment is the main method for perianorectal abscesses in clinical medicine. However, the location, number, specific shape of the abscess cavity, and its relationship with surrounding muscles of perianorectal abscess have a direct impact on the choice of surgical methods, which in turn will influence its prognosis [30]. Therefore, it is very important to pay attention to the preoperative diagnosis of such patients for the implementation of targeted and effective surgical treatment. Therefore, by using DTI MRI imaging sequences, we can scan the internal opening, the degree of infection and infiltration, the extent of abscess, and the relationship between the erosion of perianal tissues and muscles, to explore a new imaging method for the evaluation and diagnosis of perianal abscess. This approach can explore the application value of DTI in the diagnosis of perianal abscess. It can improve the accuracy of preoperative evaluation, reduce damage to the anal sphincter, reduce the recurrence rate, and improve the quality of life of patients.

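### The structured report blends imaging with operative findings and is then compared between arms, so it cannot show which imaging test is more accurate

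*Protocol article*

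**What the plan says.** All references are to the protocol article.

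- **Structured Imaging Report:** the report "serves as a synthesis of direct intraoperative findings and preoperative DTI results". The surgeon documents the anatomy during the operation, and "These surgical observations are then integrated with the preoperative DTI interpretations provided by a senior radiologist" to finalise one report. The section adds that "this report is compiled postintervention and therefore does not inform real-time intraoperative decisions". Table 1 agrees, placing the report immediately after the operation.
- **Treatment Plan:** "the control group receives conventional DWI, whereas the intervention group undergoes DTI".
- **Study Design and Statistical Plan:** structural characteristics are compared between the two groups, and "categorical items from the structured report will be compared using chi-square test or Fisher exact test". Continuous items get t tests or Mann-Whitney tests.
- **Objectives of the Study:** one aim is to "improve the accuracy of preoperative evaluation".
- **Discussion:** through the structured report, "we aim to determine whether the test under consideration is effective and which of the 2 tests is more effective".
- **Abstract (Methods):** the report is described as resting on imaging and covering location, number, course of the cavity, thickness and relation to muscle. Operative findings are not mentioned.
- **Randomization:** in both arms the surgeon reads an imaging report before operating. That report is not listed as an outcome.

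**The concern.** Accuracy is a property of an imaging reading set against the truth in the same patient, and here the natural truth is what the surgeon finds. The plan departs from that in three ways.

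1. The imaging reading and the operative finding are combined in one record after surgery. As described, what the imaging alone showed is not kept as a separate outcome.
2. The comparison is of how often each item is reported in each arm. True anatomy is balanced in expectation by randomisation, so this is not a comparison of right and wrong readings.
3. The only imaging input named is DTI, which controls do not have. Either the control report is built differently, or an unstated substitute is used. Both leave room for a difference that comes from how the form was filled in.

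At stake is the diagnostic objective. Followed as written, the plan yields a set of P values that do not bear on which test reads the anatomy more accurately.

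**Working it through.** The plan gives no figure to reproduce here, so the check is a reading of the sections against each other, an illustration, and a precision calculation for the alternative.

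**Step 1. The sections side by side.** The Abstract has a report based on imaging. The Structured Imaging Report section has a postoperative synthesis of surgery and DTI. The Discussion has a report based on DTI images that is to rank the two tests. The Treatment Plan gives DTI to one arm only. No section plans agreement, sensitivity or specificity of each arm's preoperative reading against surgery.

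**Step 2. What a comparison of item frequencies can show.** Take one yes/no item with true prevalence π, equal in both arms in expectation. Let w be the weight that the merged report gives to the surgical finding. Then

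P(item reported) = (1 − w)·[π·sens + (1 − π)·(1 − spec)] + w·π.

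Prevalence, sensitivity, specificity and w are assumptions; none is in the document. Test A has sensitivity and specificity 0.95/0.95, and test B has 0.75/0.75. Power is for 45 per arm, two-sided α 0.05.

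| π | w | Test A | Test B | Difference A − B | Power |
|---|---|---|---|---|---|
| 0.5 | 0 | 0.5×0.95 + 0.5×0.05 = 50% | 0.5×0.75 + 0.5×0.25 = 50% | 0 | none beyond α |
| 0.3 | 0 | 0.3×0.95 + 0.7×0.05 = 32% | 0.3×0.75 + 0.7×0.25 = 40% | −8 points | about 12% |
| 0.7 | 0 | 0.7×0.95 + 0.3×0.05 = 68% | 0.7×0.75 + 0.3×0.25 = 60% | +8 points | about 12% |
| 0.3 | 0.5 | 0.5×0.32 + 0.5×0.30 = 31% | 0.5×0.40 + 0.5×0.30 = 35% | −4 points | about 6% |
| any | 1 | π | π | 0 | none beyond α |

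With a second pair, 0.95/0.95 against 0.80/0.90, the gaps at w = 0 are 1, 5 and 9 points at prevalence 0.3, 0.5 and 0.7. Power is at most about 14%.

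Two things follow. A large gap in accuracy can give no difference in frequencies. When there is a difference, its sign depends on prevalence: the better test reports the item less often at 0.3 and more often at 0.7. The direction therefore does not identify the better test. Adding surgical input shrinks the gap further.

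**Step 3. Precision of a per-patient agreement comparison.** Half-width of the 95% CI for a risk difference = 1.96·√[p₁(1 − p₁)/n + p₂(1 − p₂)/n], with n = 45. Agreement rates are assumed.

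- 90% vs 75%: 1.96·√[(0.09 + 0.1875)/45] = 0.154.
- 90% in both arms: 1.96·√[(0.09 + 0.09)/45] = 0.124.
- 75% in both arms: 1.96·√[(0.1875 + 0.1875)/45] = 0.179.

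If none of the 37 patients enrolled by January 2026 could be used, 90 − 37 = 53 would remain, or about 26.5 per arm if split evenly. At 90% vs 75% the half-width is then 1.96·√(0.2775/26.5) = 0.201.

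**The case against.** The best case for the plan has five parts.

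- **DTI may be shorthand.** Both arms have a preoperative imaging report and the comparison is planned in both, so DTI in the report's definition may mean the allocated sequence. This is plausible. A reader might infer that the control report cannot be completed at all; the text does not establish that. It does need reconciling.
- **The form may keep the sources apart.** Table S1 is in an appendix not shown and may have separate imaging and surgical fields. This cannot be excluded. Even so, the article describes one integrated, finalised report and plans no test of one source against the other.
- **Frequencies are not always uninformative.** Where imaging contributes, reported rates can differ because detection differs, as step 2 shows. So the comparison is not empty in every case. It is weak, and its sign cannot be read as accuracy.
- **Effectiveness is not accuracy.** The Discussion says effective, and randomised recurrence addresses that. This stands for the primary endpoint. But the sentence assigns the question to the structured report, and the Objectives name accuracy.
- **Agreement is imprecise too.** At the assumed 90% vs 75%, the interval would run from 15 − 15.4 to 15 + 15.4 points and would just include zero. This is true, but the estimate would at least be of the right quantity.

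Two stronger readings are tempting. One is that agreement between imaging and surgery becomes 100% by construction in both arms. That is only the limiting case where surgery overrides imaging everywhere; the document says the sources are integrated, and controls have no DTI reading that could agree. The other is that the reliability check cannot work. The article says "a subset of the completed reports will undergo independent review by a second surgeon who remains blinded to the initial assessment". What is masked is not spelled out, but blinding is stated, and the detail may lie in the full protocol.

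**Conclusion.** The concern holds. As built and analysed, the structured report cannot show which imaging test is more accurate, whether or not the arms differ on its items. The reference standard is merged into the index-test record, and the contrast is between item frequencies that randomisation balances in expectation. The descriptions in the Abstract, Structured Imaging Report and Discussion also disagree on what the report contains, and the control arm's imaging input is not stated.

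The argument rests on the text. The size shown (0 to 9 points across the assumed accuracies, with power of at most about 14%) is illustrative and depends on assumed prevalence and accuracy. The reach is limited: this is one secondary outcome, and the 6-month recurrence endpoint does not use the report and is not affected.

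**What to change.** 1. Reconcile the Abstract, Structured Imaging Report and Discussion, and state that the imaging input is the allocated sequence, DTI or DWI.
2. Record the preoperative reading on the same items in both arms and lock it before incision.
3. Record the surgeon's operative findings on a separate form with the same items.
4. For each patient, score agreement between the two records, and compare the proportion agreeing between arms as a risk difference with a 95% CI. Let this replace the tests on raw anatomical items.

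**Cost.** The case report form is split and the analysis text revised. No new staff, scan or visit is needed: a preoperative imaging report already exists in both arms, and the surgeon already documents findings.

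**Downsides to state.** The surgeon has seen the images, so agreement will be somewhat inflated in both arms. Precision is limited: about 15 points either side at 90% vs 75%, and 12 to 18 over the assumed range. Patients already enrolled can be included only where their existing preoperative reports cover the items. The document does not show that they do, and the Discussion says there is no uniform measurement standard. If all 37 were lost to this analysis, the half-width would be about 20 points, which is a reason to make the change soon.

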#### Postoperative Pain Score

Pain scores: The visual analog scale is being used to measure postoperative pain on days 3 and 7 [20]. Participants are asked to draw a horizontal line on a piece of paper, with 0 at one end representing no pain and 10 at the other end representing severe pain. Participants then mark a point on the line corresponding to the intensity of their pain sensation. The distance from point 0 to the marked point is measured to determine the pain intensity score.

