### Sample Size Calculation

The sample size was calculated based on data from a preliminary pilot study involving 20 patients with perianal abscesses (10 in each preliminary subgroup). Previous studies have reported an overall postoperative recurrence rate for perianal abscess of approximately 11.7% [17]. In the pilot study, the 6-month postoperative recurrence rate was 15% among patients who underwent conventional MRI–guided surgical treatment, while the recurrence rate was 5% in those who received preoperative DTI assessment combined with targeted surgical intervention. Using a 2-sided α level of .05 and a β level of .20, the sample size for the intervention (DTI group) and control (conventional MRI group) was estimated using Power Analysis and Sample Size software (version 11), resulting in N1=N2=41. Considering a 10% potential attrition rate during follow-up, the required sample size for each group was adjusted to 45 (41/0.9), leading to a total enrollment of 90 participants for the formal study.

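### The pain scale is described as a line each participant draws, with no stated length and no conversion to 0-10, so the wording permits scores on unequal scales

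*Protocol article*

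**What the plan says.** The Postoperative Pain Score section describes the measurement step by step. The instrument and timing are given as "The visual analog scale is being used to measure postoperative pain on days 3 and 7". The line itself comes from the patient: "Participants are asked to draw a horizontal line on a piece of paper, with 0 at one end representing no pain". The opposite end carries the label 10, for severe pain. The patient then places a mark somewhere along the line, and the scoring rule is: "The distance from point 0 to the marked point is measured to determine the pain intensity score".

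Neither this section nor any other gives a line length, a preprinted form, a unit for the distance, or a rule for turning the distance into a value between 0 and 10.

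The Statistical Plan treats the result as a continuous outcome: "postoperative visual analog scale pain scores will be evaluated with a linear mixed model to assess group, time, and interaction effects". Results are to be reported as estimated marginal means and mean differences with 95% confidence intervals.

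**The concern.** A visual analog score is comparable between people only if the line has one known length or the mark is expressed as a fraction of the line. The labels 0 and 10 name the two ends but do not fix the distance between them. If the participant makes the line and the distance is what is measured, the score reflects both how much pain there is and how long a line was drawn.

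Three things are at stake in the planned model:

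- Variation in line length between patients adds variance to the group contrast.
- Variation within a patient between days 3 and 7 adds error to the time and interaction effects.
- The mean difference is expressed in an unclear unit. If the average line is not 10 cm, the difference is stretched or shrunk in proportion.

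The article does not merely leave out a detail here. It states a procedure, and that procedure followed literally does not produce a common scale. An analysis plan could not repair this afterwards if line lengths cannot be recovered.

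**Working it through.** The documents state no numerical figure for this outcome (no line length, SD, effect size or power), so there is nothing to reproduce. The check has two parts.

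**1. Does the stated rule give a common scale?**
Let p be the relative position of the mark (0 to 1) and L the line length in cm. The measured distance is p × L. The rescaled score is 10 × (p × L) / L = 10p. For p = 0.40:

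| Line length (cm) | Measured distance | Rescaled score |
|---|---|---|
| 6 | 0.40 × 6 = 2.4 | 4.0 |
| 8 | 0.40 × 8 = 3.2 | 4.0 |
| 10 | 0.40 × 10 = 4.0 | 4.0 |
| 12 | 0.40 × 12 = 4.8 | 4.0 |
| 15 | 0.40 × 15 = 6.0 | 4.0 |

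The distance in cm agrees with the 0-10 labels only when the line is 10 cm long. The text does not ensure that, and it states no division by L.

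**2. How much noise could this add?**
All inputs except the group size are assumptions. True score on 0-10: mean m = 2 to 5, SD s = 2. Line length relative to 10 cm: mean 1, coefficient of variation c = 10%, 20% or 30%, independent of pain. For a single visit:

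Var(distance) = (s² + m²)(1 + c²) − m²

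so the variance ratio against a fixed line is 1 + c²(1 + m²/s²).

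Example, m = 5, c = 0.20: (4 + 25)(1.04) − 25 = 5.16, and 5.16 / 4 = 1.29. Example, m = 2, c = 0.20: (4 + 4)(1.04) − 4 = 4.32, and 4.32 / 4 = 1.08.

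| Assumed mean | c = 10% | c = 20% | c = 30% |
|---|---|---|---|
| 2 | 1.02 | 1.08 | 1.18 |
| 3 | 1.03 | 1.13 | 1.29 |
| 4 | 1.05 | 1.20 | 1.45 |
| 5 | 1.07 | 1.29 | 1.65 |

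Expressed as an equivalent loss of patients, 1 − 1/ratio, the c = 20% column runs from 1 − 1/1.08 = 7% to 1 − 1/1.29 = 22%.

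To put this in terms of power, take 41 evaluable per arm (Sample Size Calculation: "resulting in N1=N2=41") and an assumed true difference of 1.25. By the normal approximation, power = Φ(1.25 / (SD × √(2/41)) − 1.96). A fixed line with SD 2 gives 0.81. With measured distances and means of 3 to 5, power is 0.78 to 0.80 at c = 10%, 0.70 to 0.76 at c = 20%, and 0.60 to 0.70 at c = 30%.

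These are single-visit figures. The planned model uses two visits, and its loss depends on how line length behaves within a patient. If length varies independently between days 3 and 7, the added error partly averages out of the group effect but falls fully on the time and interaction effects. If each patient draws a similar line both times, the reverse holds: the group contrast keeps the extra between-patient variance and the change over time is disturbed less.

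**The case against.** The strongest reply is that scoring by raw distance is an inference. The section labels the far end of the line 10 and says the distance is measured in order to determine the score; it does not say that the score equals the distance in centimetres. A 10-cm line or a rescaling may be what was meant, and the verb for drawing may be a slip for a line handed to the patient. A reader might infer that centimetres are definitely entered as scores and that values above 10 will occur. The text does not support that: a mark at the far end is labelled 10 whatever the length. This part of the objection stands, and the point is therefore about what the wording permits.

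A second reply is that line length and form design belong in a full protocol or case report form and may fairly be left out of an article. That would hold if the article were silent. It instead describes a participant-drawn line and a distance-based score, and that description needs correcting whichever practice is in use.

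A third reply is that the size depends heavily on an unknown mean. This also stands. Quoting only the result at mean 5 and a 20% coefficient of variation (about 30% more variance, or more than a fifth of patients lost) would mislead, since at mean 2 the corresponding figures are 8% and 7%.

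**Conclusion.** The point holds as a badly specified measurement procedure for a secondary outcome. Followed literally, it allows identical relative pain to give different scores between patients or visits, adds noise to the mixed model, and leaves the unit of the reported mean difference unclear.

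The size cannot be fixed from the documents. Under the assumptions shown (SD 2, mean 2 to 5, line-length coefficient of variation 10% to 30%, length independent of pain), single-visit variance rises by about 2% to 65%, and by 8% to 29% at a coefficient of variation of 20%.

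A reader might also infer that the treatment comparison is biased. The documents do not support that. Allocation is random, and the Blinding section keeps both participants and outcome assessors unaware of group, so line length should not differ systematically by arm. The primary endpoint, recurrence at 6 months, is unaffected.

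**What to change.** Specify a preprinted horizontal line of fixed length, for example 100 mm, with the same printed anchors on days 3 and 7. Define the score as 10 × (distance to mark / total line length), and state that this value enters the mixed model. Where sheets from patients already scored were kept, measure both lengths and apply the same formula. If a fixed printed line is already in use, correct the description in the Postoperative Pain Score section and state its length.

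The cost is a printed form, a sentence or two of text and re-measurement of stored sheets. The limitation is that scores whose sheets were not kept cannot be rescaled; the documents do not say whether they are kept. The Results section reports 37 of 90 participants enrolled as of January 2026, with recruitment continuing to October 2026, so at that date 90 − 37 = 53 participants could still be scored on a fixed line from the outset.
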